## Summary of Statistical Analysis Plan Modifications

Before beginning any analysis, we felt it necessary to revisit outcomes and provide a more detailed/thorough analysis plan to ensure both were as complete as possible. The analysis plan was updated to be more descriptive of the specific comparisons that would be made, to include communication modality and demographics.

## Appendix A: Final Interview Guides

### Support BP Interview Protocol – Provider

\*\*Indented bullet points are potential probes

#### Introduction/Description

SupportBP is a study comparing the effectiveness of different approaches to improving blood pressure control amongst patients with hypertension. The study used remote monitoring of blood pressure readings and medication adherence through text messaging as well as the inclusion of a support partner engaged in “facilitated cheerleading” to provide motivation to the patient. The questions I would like to ask focus on the provider’s experience with SupportBP. I will ask you to talk about your personal response to SupportBP encounters and your overall perception of the intervention from a provider perspective. Our intention is to improve the program for future iterations based on both patient and provider feedback.

Your participation in this study is confidential. With your permission, this interview will be recorded to accurately keep track of information, but the recording will be deleted at the completion of the study. Your participation in this study is important. However, if you would wish to stop at any time, you may do so without any consequence to you. Additionally, feel free to ask me any questions concerning the interview or the study as we proceed. May we begin?

#### Clinical Care Background for Hypertension Patients

- Describe how you typically manage the blood pressure of your hypertensive patients.
  - Additional probes: How often do you have hypertension patients return for visits? Do you ask patients to monitor their blood pressure at home? Do you give patients a blood pressure cuff during the appointment or are they responsible for acquiring one? Do patients log their blood pressure measurements over time?
- What is the patient’s role in managing hypertension?
  - Rephrase: What are your expectations of your patients in regard to monitoring their blood pressure?
- How do patients track their blood pressure outside of office visits and how do the patients communicate this information to you?
  - Rephrase: How do you communicate with your patients regarding their blood pressure monitoring and medication adherence?
- What criteria do you use to decide when to elevate a patient’s blood pressure medication?

#### Overall Perceptions of SupportBP

- What are your overall perceptions of SupportBP?
- Tell me about the impact of SupportBP on your patient’s blood pressure control.
- How did this program affect your work flow and clinical practice?
- How do you want to receive this information? Do you want to receive the encounters or would you prefer that someone else receives it?
- How much do you want the program to manage and do in terms of adjusting medication and communicating with the patient?
  - How much involvement would you as the physician prefer to have?

### **Future Improvements**

- How can this program be improved for the patients?
- How can this program be improved from providers?
  - If we don't want to separate question for patients/providers: In future iterations of this intervention, what improvements would you make?
- Please name three things you like and dislike about SupportBP.

## **Support BP Interview Protocol – Nurse Pool**

\*\*Indented bullet points are potential probes

### **Introduction/Description**

SupportBP is a study comparing the effectiveness of different approaches to improving blood pressure control amongst patients with hypertension. The study used remote monitoring of blood pressure readings and medication adherence through text messaging as well as the inclusion of a support partner engaged in “facilitated cheerleading” to provide motivation to the patient. The questions I would like to ask focus on the provider’s experience with SupportBP. I will ask you to talk about your personal response to SupportBP encounters and your overall perception of the intervention from a provider perspective. Our intention is to improve the program for future iterations based on both patient and provider feedback.

Your participation in this study is confidential. With your permission, this interview will be recorded to accurately keep track of information, but the recording will be deleted at the completion of the study. Your participation in this study is important. However, if you would wish to stop at any time, you may do so without any consequence to you. Additionally, feel free to ask me any questions concerning the interview or the study as we proceed. May we begin?

### **SupportBP Encounter Response**

- Describe the process of response to a SupportBP encounter.
  - Additional probes: Who typically responded to the encounter? What steps were taken when an encounter was received? Was the patient contacted after an encounter was received, and, if so, how was this communication structured?
- How was communication between the nurse pool structured?
- Was there communication with the patient’s physician throughout the intervention?
  - At what point was the physician looped into the response, if at all?
- How much time did these responses require each daily/weekly?

### **Overall Perceptions of SupportBP**

- What are your overall perceptions of SupportBP?
- Tell me about the impact of SupportBP on your patient’s blood pressure control.
- How did this program affect your work flow?
- How do you want to receive this information? Do you want to receive the encounters or would you prefer that someone else receives it?
- How do you feel about the number of people that were responsible for responding to SupportBP encounters?
  - Rephrase: Would you say that the number of people in the nurse pool was sufficient for effectively responding to the encounters?

### **Future Improvements**

- How can this program be improved for the patients?
- How can this program be improved from providers?
  - If we don’t want to separate question for patients/providers: In future iterations of this intervention, what improvements would you make?
- Please name three things you like and dislike about SupportBP.

## **Support BP Interview Protocol – Nurse Practitioner**

\*\*Indented bullet points are potential probes

### **Introduction/Description**

SupportBP is a study comparing the effectiveness of different approaches to improving blood pressure control amongst patients with hypertension. The study used remote monitoring of blood pressure readings and medication adherence through text messaging as well as the inclusion of a support partner engaged in “facilitated cheerleading” to provide motivation to the patient. The questions I would like to ask focus on the provider’s experience with SupportBP. I will ask you to talk about your personal response to SupportBP encounters and your overall perception of the intervention from a provider perspective. Our intention is to improve the program for future iterations based on both patient and provider feedback.

Your participation in this study is confidential. With your permission, this interview will be recorded to accurately keep track of information, but the recording will be deleted at the completion of the study. Your participation in this study is important. However, if you would wish to stop at any time, you may do so without any consequence to you. Additionally, feel free to ask me any questions concerning the interview or the study as we proceed. May we begin?

### **Clinical Care Background for Hypertension Patients**

- Describe how you typically manage the blood pressure of your hypertensive patients.
  - Additional probes: How often do you have hypertension patients return for visits? Do you ask patients to monitor their blood pressure at home? Do you give patients a blood pressure cuff during the appointment or are they responsible for acquiring one? Do patients log their blood pressure measurements over time?
- What is the patient’s role in managing hypertension?
  - Rephrase: What are your expectations of your patients in regard to monitoring their blood pressure?
- How do patients track their blood pressure outside of office visits and how do the patients communicate this information to you?
  - Rephrase: How do you communicate with your patients regarding their blood pressure monitoring and medication adherence?
- What criteria do you use to decide when to elevate a patient’s blood pressure medication?

### **Overall Perceptions of SupportBP**

We will ask about your perceptions of both the first round of the program as a provider with patients enrolled in the study and the second round with the encounters routed to the nursing pool.

#### **First Round – Provider**

- What are your overall perceptions of SupportBP in the first round prior to the encounters being routed to the nursing pool?
- How did this program affect your work flow and clinical practice in the first round?
- Tell me about the impact of SupportBP on your patient’s blood pressure control in the first round.
- How do you want to receive this information as a provider?
- How much do you want the program to manage and do in terms of adjusting medication and communicating with the patient?
  - How much involvement would you as the provider prefer to have

## **Second Round – Nursing Pool**

- What are your overall perceptions of SupportBP in the second round with the encounters being routed to the nursing pool?
- How did this program affect your work flow and clinical practice in the second round?
- Tell me about the impact of SupportBP on your patient's blood pressure control.
- Do you want to continue to receive the encounters or would you prefer that someone else receives it?
- Comparing first round to second round, what are your perceptions of how other physicians regarded the program with the change in workflow to direct all encounters to the nursing pool?
- What could be improved regarding communication between the clinicians and the SupportBP program?

## **Future Improvements**

- How can this program be improved for the patients?
- How can this program be improved for providers?
- What would need to be changed about SupportBP in order to be a clinically practical intervention using the nursing pool model?
- Please name three things you like and dislike about SupportBP.

## **Additional Questions for [name] – Vice Chair for Clinical Operations**

Frame: unique position so we want to ask you some specific questions addressing that position. Asking based on all of the feedback that he heard.

- What was the general perception of SupportBP amongst the physicians in the practice?
  - Would you say that most clinicians had a positive or negative experience with SupportBP?
- How did the perception of SupportBP change after switching to the nurse pool model?
- What could be improved regarding communication between the clinicians and the SupportBP program?
- What would need to be changed about SupportBP in order to be a clinically practical intervention based on clinician feedback?

## Appendix B: Final Text Message Content

### Weekly Text Messaging Content (Repeated Weekly)

|                                                              | Day 1 | Day 2 | Day 3 | Day 4 | Day 5 | Day 6 | Day 7 |
|--------------------------------------------------------------|-------|-------|-------|-------|-------|-------|-------|
| BP Measurement                            | X     |       | X     |       | X     |       |       |
| BP Feedback                                           |       |       |       |       |       | X     |       |
| Medication Adherence                                  |       |       |       | X     |       |       |       |
| Medication Feedback                                   |       |       |       | X     |       |       |       |
| Support Partner Msg
(to partner, SS arm only)      |       |       |       |       |       |       | X     |
| Support Partner Feedback
(to Patient, SS arm only) |       |       |       |       |       |       | X     |

 BP Measurement prompts sent at 8am. If no response by 7pm, a reminder was sent. Patients had 24 hours to respond to each prompt.

### Welcome

Arms: as below

Begin: Day 0

Repeats on days: does not repeat

At: upon randomization

- Arms 1 & 2:
  - “Welcome to SupportBP, PARTICIPANT\_FIRSTNAME! You’ll receive your welcome packet, blood pressure cuff & instructions within about a week, and your first texts will start shortly after that. Questions? Call [contact] or email [contact]”
- Arm 3:
  - “Welcome to SupportBP, PARTICIPANT\_FIRSTNAME! You’ll receive your welcome letter within about a week. Questions? Call [contact] or email [contact]”

### BP Reminders

Arms: 1& 2

Begin: Day 8

Repeats on days: 8, 10, 12, 15, 17, 19, 22, 24, 26, 29, 31, 33, 36, 38, 40, 43, 45, 47, 50, 52, 54, 57, 59, 61, 64, 66, 68, 71, 73, 75, 78, 80, 82, 85, 87, 89, 92, 94, 96, 99, 101, 103, 106, 108, 110, 113, 115, 117

At: 8am

- “What is your blood pressure today? (Ex. 120/80)
  - If valid input <180/110 received, “{systolic/diastolic} has been recorded. Thank you.”
  - If valid input >180/110 received, “Your blood pressure ({systolic\_value}/{diastolic\_value}) is elevated. Please wait 15 minutes and check it again. If the top number is still higher than 180 -OR- the bottom number is still higher than 110, please come in to the office (Penn Family Care: [name]) for a blood pressure check with a nurse during normal office hours. “ \*

- If input format incorrect, "Sorry, we do not understand that response. Please input BP in the following format: 120/80. Questions? Call [contact]."
  - If no input received, no response.
- \* An alert will also be sent to the Research Coordinator to follow-up with participant by phone and alert the patient's PCP via PennChart.

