**Randomization:** The coordinator will use the Way to Health web platform to randomize patients into this study. Patients will be randomized into 1 of the 3 study arms (ratio 2:2:1) in variable blocks of 5 and 10. After randomization occurs, the study coordinator will inform the patient of the randomization group they have been assigned into. Arms **A-1** and **B-2** will receive a blood pressure cuff and bidirectional text messaging regarding blood pressure and medication adherence. Arm **B-2** will also include a social support partner to participate. Arm **C-3** will receive usual care. After randomization occurs, the study coordinator will inform the patient of the randomization group they have been assigned into. Those patients assigned to Arms **A-1** and **B-2** (remote monitoring) will be shipped the blood pressure cuff with instructions for use and a number to call us with questions. If we do not receive blood pressure readings from the patient ~~5-10~~ days after the patient received the package, a coordinator will call the patient to make sure the device is working properly. The coordinator will also reach out to the feedback partner in the social support arm to include in Way to Health.

**Monitoring:** **Participants in Arms 1 and 2 will be asked to submit blood pressure measurements three times each week for the duration of the study. If at any point, 3 out of the last 10 reported BP measurements are elevated, the elevated measurements and any measurements between (up to 10, with a minimum of 5 if available), will be reported to the Nursing Pool PCP via a medical record encounter. This encounter will also reference the flowsheet so the care team may view all patient submitted measurements to date, if needed or desired. Information about self-reported medication**

adherence will also be reported ~~to the PCP~~ at this time. Nursing pool staff will meet twice weekly with an assigned Nurse Practitioner (NP) to review all monitoring notification sin bulk, and make appropriate medication adjustments with follow-up with the patient as needed. The final encounter will be routed by the nursing pool to the PCP as an FYI. Measurements will be reported again in this same manner if they remain elevated and 3 weeks have elapsed since last reported.

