Additionally, if a participant in Arm 1 or Arm 2 submits any single elevated blood pressure measurement ( $\geq 180$  and/or  $\geq 110$ ), this measurement along with information about self-reported medication adherence will be reported to the Nursing Pool ~~PCP~~ via a medical record encounter and the same procedure as outlined above will be followed for proper patient follow-up.

Follow-Up Visit: During the enrollment call the research coordinator will assign the patient a date for their follow-up blood pressure measurement at the end of the 4 month intervention. The coordinator will assign the follow-up date in the hopes that using an opt-out method (assign the follow-up date to the patients) rather than an opt-in method (allow the patient to select their follow-up date) will increase attendance. However, the patient can change their follow-up date at any time. The intervention of the study will be 4 months from date of consent, and an additional ~~3-8~~ months of follow-up, passively monitoring visit utilization and blood pressure in the electronic medical record. At the conclusion of the intervention, participants will receive an additional \$50 to complete an in-person blood pressure measurement and post-study survey. Patients will receive a letter one month prior to the follow-up appointment, and a text 2 weeks prior, ~~and 3 days prior,~~ **and 1 day prior** to the appointment as a reminder of their appointment. The messages will be a reminder of the appointment date, time and location, **as well as of the incentive for completion of the visit.** Patients will also be instructed to call us if they would like to change their appointment. Information about BP measurements will be recorded in EPIC and message will be sent to the **Nursing Pool and PCP** with the research BP measurement included. When patients attend their follow-up measurement they will also be asked to complete a short follow-up survey. If a patient does not attend their in-person follow-up measurement, a coordinator will call the patient to **reschedule the visit and if that is not possible, to** complete the survey over the phone.

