## **Potential Study Risks**

As this study does not involve any medical decision making and only tests the use of social behavioral approaches to encouraging patients to use evidence-based treatments that their providers have prescribed to treat high blood pressure, we consider this study minimal risk. The primary risk would be from a breach of confidentiality involving medical records reviews and monitoring of hypertension medication and blood pressure adherence with text messaging which will be maintained on the Way to Health platform. This risk has been mitigated by extensive privacy protection protocols, a highly secure data storage system, and a plan to remove identifiers from the data wherever possible. In addition, all personnel will be held to high standards of upholding confidentiality and safeguarding patient privacy.

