| 02/06/2018         | 1) Updating study personnel
2) New/Updated patient materials                                                                                                                                                                                                                              | 1) Remove 2 research assistants no longer working with study team
2) A. Welcome letters (2, updated) – provides additional language with more detailed information about high and low blood pressure readings. This language was not added to the control group welcome letter since they are not being monitored
2) B. Introductory letter (new) – letter mailed with informational brochure ahead of recruitment phone call                                                                                                                                                                                                   | 2/14/18       |
| 02/27/2018         | 1) Adding blood pressure monitoring instruction sheet from AHA
2) Add link to blood pressure monitoring video to Welcome letter
3) Updating text message content
4) Adding partner enrollment script/consent language
5) Protocol Changes: Updating Inclusion/Exclusion criteria | 1) A .pdf infographic from the American Heart Association depicting proper home blood pressure monitoring
2) Adding link to a video on proper home blood pressure monitoring from Mayo Clinic
3) Edits to existing automated messaging around severely elevated BP measurements
4) Scripting to be used when contacting participant support partners
5) Updates to inclusion/exclusion criteria (2): increase from 2 visits in past year to two visits in two years; remove exclusion for liver cirrhosis                                                                                                                 | 3/30/18       |

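### The risk section says no medical decisions are involved, yet Arms 1 and 2 include study-prompted medication adjustment, only high readings trigger review, and no by-arm outcome names hypotension or treatment-related harm

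*Supplement*

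**What the plan says.** Final Protocol, Potential Study Risks, opens its minimal-risk argument with "As this study does not involve any medical decision making and only tests the use of social behavioral approaches" and then names a confidentiality breach as the primary risk. It mentions no risk from treatment.

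Final Protocol, Procedures (Monitoring), describes what happens to readings in Arms 1 and 2. A report goes to the nursing pool if "3 out of the last 10 reported BP measurements are elevated", or if a participant "submits any single elevated blood pressure measurement" (at or above 180 systolic and/or 110 diastolic). Pool staff meet a nurse practitioner twice a week to review the notifications and "make appropriate medication adjustments with follow-up with the patient as needed".

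Appendix B, BP Reminders, has two replies for valid readings. "If valid input <180/110 received" leads to an acknowledgement that the value was recorded. "If valid input >180/110 received" leads to a recheck and office-visit message, with an alert to the research coordinator, who follows up and alerts the PCP.

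Low readings are mentioned in one place. The modification log (02/06/2018) says the updated welcome letter for the monitored arms "provides additional language with more detailed information about high and low blood pressure readings". The letter itself is not in the supplement.

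Final Protocol 1.6 and the Final SAP 1.2 list SBP, DBP, normotensive status, adherence, EHR blood pressure by arm, visits, calls, hospitalizations and medication changes. Neither names hypotension, syncope, falls or medication-related harm.

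**The concern.** Two parts of the final protocol describe different studies. The risk section describes a behavioural intervention in which treatment decisions play no part. The Monitoring procedure describes a pathway in which the study collects readings, selects which to send, and sends them to staff who adjust medication. The log gives the same purpose: the 06/06/2018 entry says PCPs are notified of uncontrolled readings so that medication can be adjusted, and the 11/30/2018 entry says patient-reported readings may be critical to adjusting it.

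Once medication adjustment belongs to the pathway, over-treatment is a foreseeable risk alongside confidentiality. The plan collects blood pressure three times a week in Arms 1 and 2, but its triggers look only upward and its outcome list has no counterpart on the low side. If SBP falls more in Arms 1 and 2 than in usual care, a reader of the results will ask what that cost in low-pressure events, and the plan has no table prepared to answer.

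**Working it through.** No figure in the plan bears on this point, so the check sets the sections side by side and traces the message rules.

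**Step 1. Risk statement against procedure.** Potential Study Risks says no medical decisions are involved. Procedures (Monitoring) has staff adjust medication after a study report. Procedures (Encounter Handling) then reviews care-team actions after those reports, medication changes among them. Both statements stand in the final text, and they cannot both be true.

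**Step 2. Direction of each trigger.**
- Three of the last ten readings elevated: upward. The Monitoring text gives no number for elevated, but whatever the cut-off, the rule looks upward.
- Single reading at or above 180 and/or 110: upward.
- Appendix B alert above 180/110: upward.

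No trigger is stated for a low reading.

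**Step 3. Trace of example readings.** Assumptions: the lower branch needs both components below its limits. The upper branch needs either component above, as the recheck wording in the reply suggests.

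| Reading | Appendix B reply | Single-reading report under Monitoring |
|---|---|---|
| 70/40 | receipt | no |
| 85/50 | receipt | no |
| 95/60 | receipt | no |
| 120/80 | receipt | no |
| 145/92 | receipt | no (may count toward 3 of 10) |
| 179/109 | receipt | no (may count toward 3 of 10) |
| 180/100 | no branch | yes |
| 170/110 | no branch | yes |
| 180/110 | no branch | yes |
| 185/95 | elevated message | yes |
| 190/115 | elevated message | yes |

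A reading of 70/40 is handled exactly like 120/80. The trace also exposes a boundary mismatch: Appendix B uses strict inequalities and Monitoring uses at-or-above. A reading with one component exactly at its limit and the other not above its own therefore has no text reply, yet must be reported.

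**Step 4. Exposure.** Appendix B lists 48 prompt days (days 8 to 117; 16 weeks × 3). Arms 1 and 2 have an accrual target of 100 + 100 = 200. Prompts: 48 × 200 = 9,600 at most. This is a ceiling on prompts. It does not estimate low readings, whose frequency the documents do not give.

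**Step 5. Outcomes.** EHR blood pressure, visits, calls, hospitalizations and medication changes are planned by arm or without restriction to an arm. None is classified by cause, so medication-related harm cannot be separated from the rest. The encounter review exists only where a monitoring report was sent, so it cannot supply usual-care figures. The EHR extraction covering all arms can.

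**The case against.** The strongest reply is that low readings are not lost. For Arms 1 and 2 the enrolment message carries an order for review of submitted readings through a flowsheet linked to Epic. An escalated report includes readings lying between the elevated ones and points to the flowsheet. The monitored arms' welcome letters reportedly cover low readings, and participants have a number to call. All of this stands. A reader might infer that a low reading reaches no one; the documents do not support that. What remains is narrower: a low reading does not itself set off an alert or a review.

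Other stronger readings also fail:
- That the reply tells participants a low value is normal. It only confirms receipt.
- That medication can only be intensified. The text speaks of appropriate adjustments, and clinicians may reduce treatment in usual care.
- That harm would be invisible. EHR blood pressure, hospitalizations and medication changes are tracked; only a named harm tabulation is missing.
- That the consent waiver is unfounded. Consent Process 1.1 and Waiver of Consent 1.1 rest on minimal risk and on the absence of procedures that normally need written consent. Neither cites medical decision making. The link runs only through the risk section, and the log shows the later reporting change was approved with an updated consent script.
- That all 200 participants were under the nurse practitioner pathway. The interview guides in Appendix A show a first round before encounters were routed to the nursing pool.

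The lack of a low-reading rule may be a deliberate choice by the clinical team, and the undefined term for valid input leaves room for a software floor. Neither is stated.

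**Conclusion.** The point holds in three parts.

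1. The contradiction between Potential Study Risks and Procedures (Monitoring) is plain on the final text and needs no clinical judgement.
2. All stated study triggers for review are high readings. This rests on the printed rules; the welcome letter's text and any software limits are not shown.
3. No outcome names hypotension or medication-related harm by arm, so the efficacy comparison lacks its safety counterpart.

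The size of any harm cannot be computed, because the documents give no rate of low readings or of treatment-related events. The number of participants concerned is at most 200, and fewer for the nurse practitioner pathway itself. The point does not show that anyone was harmed, that the waiver was wrong, or that a particular clinical rule is needed. It shows that the risk text does not describe the intervention delivered and that the planned reporting is one-sided.

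**What to change.** 1. Correct Potential Study Risks to say that medication adjustment is part of the Arm 1 and 2 pathway, and name its risks. Then check that the minimal-risk statements in Consent Process 1.1 and Waiver of Consent 1.1 still describe the intervention delivered.
2. Reconcile Procedures (Monitoring), Potential Study Risks, the welcome letters cited in the log and Appendix B (BP Reminders) on how low readings are handled, and settle the boundary mismatch at exactly 180 or 110. The rule is for the clinical team; none is proposed here.
3. Add to the SAP a descriptive by-arm table of hypotension, syncope or fall, and medication-related visits and hospitalizations, drawn from the EHR review planned in all arms. Use the same source and time window in each arm. State that closer contact in Arms 1 and 2 may raise detection there, so a difference should not be read directly as a treatment effect.

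The cost is a text amendment and a few more fields in a record review that is already planned. Neither the sample size nor the primary analysis changes.

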### **Data Disclosure**

Blood pressure measurements will be disclosed to the subject's primary care physician if they reach or surpass a pre-established threshold determined to be an immediate danger to the subject's health.

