# Final Statistical Analysis Plan

**\*\*New changes from initial protocol notated in bold, parts removed from initial protocol notated in strikethrough**

## Analysis Plan

### 1.1 Power and sample size

Assuming 5.3mmHg standard deviation of SBP (given variability of BP over time) and a two-sided significance level of 0.017 (to accommodate the three pairwise comparisons), our sample size of 60 in each intervention arm and 30 in the control arm provides 80% power to detect a difference in SBP reduction of 3.75 mmHg between either intervention and usual care, and a difference in SBP reduction of 3.1 mmHg between the remote monitoring and social influence arms. A preliminary data extraction shows about 2300 patients uncontrolled hypertensive patients in PFC, which should provide a sufficient population for enrollment. **However, based on additional clinical information obtained after the study was initiated, we estimate a standard deviation for change in SBP of 20mmHg, larger than our initial estimate. Thus, we increased our accrual target to 100 in each intervention arm and 50 in the control arm, which provides 80% power to detect a difference in SBP reduction of 11mmHg between either intervention and usual care, and a difference in SBP reduction of 9mmHg between the remote monitoring and social influence arms.**

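### Appendix B has no message branch for a home reading of exactly 180 systolic or 110 diastolic, although the protocol's alert includes both values

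*Supplement*

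**What the plan says.** The Final Protocol, Procedures (Monitoring), requires a report to the Nursing Pool "if a participant in Arm 1 or Arm 2 submits any single elevated blood pressure measurement". It defines elevated as systolic at or above 180 and/or diastolic at or above 110, so both limits are inclusive.

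Appendix B, BP Reminders, gives the automated replies to participants in Arms 1 and 2. A valid reading has two branches:

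- "If valid input <180/110 received": the value is acknowledged as recorded.
- "If valid input >180/110 received": the participant is told that the pressure is elevated and is asked to recheck after 15 minutes. The participant is told to come to the office "If the top number is still higher than 180 -OR- the bottom number is still higher than 110".

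A footnote attached only to the second branch adds: "An alert will also be sent to the Research Coordinator to follow-up with participant by phone". The coordinator also alerts the PCP. The remaining branches cover a wrongly formatted reply and no reply.

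The Final Protocol, Data Disclosure, says that readings "will be disclosed to the subject's primary care physician if they reach or surpass a pre-established threshold". It gives no number, but the wording is again inclusive.

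**The concern.** The protocol treats a reading exactly on either limit as needing an alert. The message script stops just below the limits and resumes just above them, and no branch covers equality. A participant who texts 180/100 has sent a reading that the protocol defines as elevated, yet the script specifies no reply.

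What is at stake is patient safety messaging. The elevated text, the recheck prompt, the coordinator's phone call and the coordinator's PCP alert all depend on the strict upper branch. The recheck sentence has the same gap. Someone who first reports 185/100 and then measures 180/100 is not told to come in, although 180 still meets the protocol alert.

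**Working it through.** This is a question of threshold logic, so there is no planned figure to reproduce.

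**Rules compared** (S = systolic, D = diastolic)

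- Protocol alert: S ≥ 180 or D ≥ 110 (Final Protocol, Procedures, Monitoring).
- Appendix B, natural reading: recorded if S < 180 and D < 110; elevated if S > 180 or D > 110. The recheck sentence supports this reading, because it joins the two components with OR.

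**Unmatched set on the natural reading**

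A reading matches neither branch when S = 180 with D ≤ 110, or D = 110 with S ≤ 180. All such readings meet the protocol alert. Readings such as 185/110 and 180/115 are still caught through the other component.

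As a check, all integer pairs with S from 100 to 220 and D from 60 to 130 were enumerated:

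- S = 180 and D = 60 to 110: 51 pairs.
- D = 110 and S = 100 to 179: 80 pairs.
- Total: 51 + 80 = 131 unmatched, all 131 meeting the protocol alert.

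These are grid cells, and the count depends on the grid. They are not a frequency.

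**Sensitivity to how 180/110 is read**

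A single inequality sign before a pair of numbers can be read in four ways. On the same grid:

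| Recorded if | Elevated if | Matches neither branch | Meets the alert but gets only the recorded reply |
|---|---|---|---|
| both below | either above | 131 | 0 |
| both below | both above | 3,791 | 0 |
| either below | either above | 1 | 130 |
| either below | both above | 61 | 3,730 |

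Every unmatched pair, under every reading, meets the protocol alert. The value 180/110 is unmatched under all four. Where recorded means either component below, 180/100 and 170/110 receive the routine thank-you reply, which is no better than silence.

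**Exposure to the rule**

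Appendix B lists 48 prompt days (16 weeks × 3). The Final SAP, section 1.1, states "we increased our accrual target to 100 in each intervention arm and 50 in the control arm", so the two monitored arms hold 100 + 100 = 200 participants. Scheduled prompts at full accrual are 48 × 200 = 9,600. This counts scheduled messages. The number of replies that fall on a limit cannot be derived from it.

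**Corrected rule**

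With elevated set to S ≥ 180 or D ≥ 110 and recorded set to S < 180 and D < 110, no pair is unmatched and none is matched twice. The elevated branch then equals the protocol alert.

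| Test reading | Current script | Corrected script |
|---|---|---|
| 179/109 | recorded | recorded |
| 180/100 | no branch | elevated |
| 170/110 | no branch | elevated |
| 180/110 | no branch | elevated |
| 181/100 | elevated | elevated |
| 170/111 | elevated | elevated |

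**The case against.** The strongest reply is that the two texts govern different actions. The protocol's limit decides when a reading goes to the Nursing Pool. It does not itself require a patient text, a recheck or a coordinator call. Those steps exist only in Appendix B and could have their own limit. That is fair as far as it goes, but a separate limit would still need to say what happens at equality, and Appendix B does not.

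The appendix's notation is also loose. Some Partner Message conditions, such as a count that must be below 1 and above 3, are impossible if read literally. The script is therefore weak evidence of what the platform actually sent. This stands, and the finding is limited to the written specification. A lost symbol in the PDF is not a convincing explanation, because the recheck sentence repeats the strict limit in words.

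Finally, other safeguards remain. The Nursing Pool reviews reported readings with a nurse practitioner and follows up with the patient as needed. A separate rule reports when 3 of the last 10 readings are elevated. The modifications log says that the welcome letters gave monitored participants more detail on high and low readings, although the letters are not shown. These limit the harm but do not replace the missing step. The Nursing Pool review is held twice weekly and in bulk, and the 3-of-10 rule addresses repeated elevated readings. The automated text is the immediate response to the participant's own reading.

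**Conclusion.** The point holds and is minor. As written, Appendix B gives no reply to some readings that the protocol defines as needing an alert. For 180/110 this is true however the branches are read. For 180/100, 170/110 and the rest of the set, it rests on the either-component reading that the script's own OR supports.

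What is lost at the limit is the elevated text, the recheck prompt and the coordinator's call and PCP alert. The Nursing Pool report remains, assuming that it runs independently of the text branch, and so does the PCP disclosure provision. The frequency is unknown. The primary outcome is the in-person 4-month systolic pressure, so its analysis, the sample size and the power are not affected.

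**What to change.** In Appendix B, BP Reminders:

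1. Set the elevated branch to systolic ≥ 180 OR diastolic ≥ 110.
2. Set the recorded branch to systolic < 180 AND diastolic < 110.
3. Reword the recheck sentence so that the participant comes in if the top number is 180 or more, or the bottom number is 110 or more.
4. Run the six test readings tabulated above through the platform and confirm the corrected results.

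As an option, name the Nursing Pool alongside the PCP in the footnote, to match the protocol's routing. The cost is two branch conditions, one sentence and a short platform test. No new data, visits or analyses are needed.
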